#### Final analysis

The primary analysis will include all participants as randomised (‘intention-to-treat’), irrespective of whether they received their allocated treatment. Both treatment effects and 95% CIs will be reported for all primary, secondary and subgroup analyses. The per-protocol analysis is a secondary analysis and will include all children without major protocol violation who had the primary outcome measured. Final analyses will be undertaken once 24-week data are available for at least 211 children in each active arm selected to continue to the second stage, and at least 422 control children. A logistic regression model with country, age, sex and oedema status as covariates, and a treatment indicator for each intervention, will be fitted. From the model, test statistics will be computed to compare each active arm to the control arm. If the test statistic exceeds the critical value of 1.904, then the corresponding arm will be identified as a promising intervention. Secondary outcomes will be evaluated using the same principles and critical values as the primary analysis. A linear regression model will be used for continuous outcomes (transformed if required); a logistic regression model will be used for binary outcomes; and a proportional hazards model will be used for time-to-event outcomes. If there are substantial missing data, the mechanism will be explored and appropriate methods (eg, multiple imputation) implemented to remove potential inference bias. Statistical code for the main analyses will be made available with the primary publication. The final trial dataset will be made open access at ClinEpiDB after the analyses in the protocol have been reported.

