**Methods and analysis:**

The Co-SAM trial is an adaptive, multicountry, phase III, individually randomised clinical trial, based on the principles that (i) interacting biological and social factors drive multimorbidity in children with SAM, and (ii) both medical and psychosocial interventions may therefore ameliorate underlying causal pathways to reduce morbidity and mortality and improve recovery. Children aged 6–59 months with complicated SAM, who have stabilised and started the transition to ready-to-use therapeutic food (RUTF), will be enrolled and randomised to one of five trial arms (standard-of-care alone; antimicrobials; reformulated RUTF; psychosocial support; or a combination of all strategies). Standard-of-care, which is provided in all trial arms, includes RUTF until nutritional recovery (defined as weight-for-height Z-score >−2, mid-upper arm circumference >12.5 cm and oedema-free since the last study visit), and other management recommended in WHO guidelines. The 12-week antimicrobial package provides daily co-formulated rifampicin and isoniazid (with pyridoxine) and 3 days of azithromycin monthly. The reformulated RUTF, which incorporates medium-chain triglycerides and hydrolysed protein to increase nutrient bioavailability and reduce metabolic stress, is provided at the same dose and duration as standard RUTF. The 12-week psychosocial package includes caregiver problem-solving therapy, educational modules, peer support groups and child play. The combined arm includes all interventions. Children start their intervention package prior to hospital discharge, with follow-up data collection in study clinics at 2, 4, 6, 8, 12 and 24 weeks. The primary composite outcome is death, hospitalisation or failed nutritional recovery within 24 weeks post-randomisation. An interim analysis will allow unpromising arms to be dropped, while the final analysis will be conducted when 1266 children have completed the study. Embedded process evaluation and laboratory substudies will explore the mechanisms of action of the interventions.

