### Sample size

For the primary analysis, a total sample size of 1266 participants across all three countries, with a final ratio of 2:1:1:1:1 in favour of standard-of-care, provides 80% power to detect a 30% reduction in the composite primary outcome of death or hospitalisation or failed nutritional recovery within 24 weeks, assuming a control arm event rate of 35% with overall one-sided alpha of 0.10 (ie, family-wise error),^32^ allowing for 5% loss to follow-up if all arms start at the same time. The control arm event rate was based on published data on mortality, readmission and nutritional recovery from the HOPE-SAM study^5 33^ in Zimbabwe and Zambia, and the Childhood Acute Illness and Nutrition network,^13 34^ which included sites in east Africa. Children who are enrolled but not randomised for any reason will be replaced.

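### The same 1266 (211 per active arm, 422 controls) is used both before and after the 5% loss allowance, so the sample size and the final-analysis trigger do not agree

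*Protocol article*

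**What the plan says.** Three places in the protocol article give the size of the trial.

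- **Sample size:** "a total sample size of 1266 participants across all three countries, with a final ratio of 2:1:1:1:1 in favour of standard-of-care". This "provides 80% power to detect a 30% reduction in the composite primary outcome", "assuming a control arm event rate of 35% with overall one-sided alpha of 0.10", and it does so "allowing for 5% loss to follow-up if all arms start at the same time". The only replacement mentioned is for children enrolled but not randomised. Nothing is said about replacing children lost after randomisation.
- **Final analysis:** "Final analyses will be undertaken once 24-week data are available for at least 211 children in each active arm" that goes on to the second stage, with at least 422 controls as well.
- **Abstract, Methods and analysis:** "the final analysis will be conducted when 1266 children have completed the study".

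The Interim analysis section gives bounds of 0 and 2.693 and an interim count of 106 participants in an active arm. The final critical value is 1.904.

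**The concern.** A total that allows for loss is a number randomised, and the number with outcomes is expected to be smaller. The Final analysis section and the abstract attach the same total to children who have 24-week data or have completed. The two uses coincide only if no child is lost, whereas the Sample size section assumes that 5% are.

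The trigger governs when recruitment can end and when the test against 1.904 is made. If all four active arms continue and some children are lost, the team will have 1266 randomised and an unmet condition. It must then either analyse below the stated trigger or enrol beyond the only total the article gives. The article does not say which. That is better settled now than late in an open-label trial.

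**Working it through.** **Inputs.** Total 1266, ratio 2:1:1:1:1, 5% loss, control rate 35%, 30% relative reduction, one-sided family-wise alpha 0.10 (Sample size); 211 and 422 with 24-week data, critical value 1.904 (Final analysis); bounds 0 and 2.693, interim count 106 (Interim analysis).

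**1. The trigger sums to the total that includes loss.** 4 x 211 + 422 = 844 + 422 = 1266.

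**2. What 1266 randomised yields at 5% loss.**
- Per active arm: 211 x 0.95 = 200.45
- Control: 422 x 0.95 = 400.9
- Total: 1266 x 0.95 = 1202.7

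The shortfall is about 10 to 11 per active arm, 21 controls and 63 overall.

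**3. What the trigger needs at 5% loss, N/(1 - 0.05).**
- Per active arm: 211/0.95 = 222.1, so 223
- Control: 422/0.95 = 444.2, so 445
- Total: 4 x 223 + 445 = 1337 (or 1266/0.95 = 1332.6, so 1333, rounding only once)

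That is 67 to 71 more than 1266.

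**4. If one arm is dropped at the interim.** Suppose it stops with 50 to 106 children and enrolment still runs to 1266, with the rest split 2:1:1:1.
- Stopped at 50: (1266 - 50)/5 = 243.2 per active arm, and 243.2 x 0.95 = 231.0 with data
- Stopped at 106: (1266 - 106)/5 = 232.0 per active arm, and 232.0 x 0.95 = 220.4 with data

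Both exceed 211. The control arm has twice as many, about 462 and 441, and exceeds 422. The Final analysis trigger is then reachable within 1266. The abstract's condition is not, because 1266 randomised with any loss never gives 1266 completers.

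**5. Does the power calculation show which meaning was intended?** The stated error rate reproduces: with bounds 0 and 2.693 at half information and 1.904 at the end, four active arms and 2:1 allocation, simulation gives a family-wise error of 0.100. For power, the treated rate is 0.35 x 0.70 = 0.245 and the difference is 0.105. With n per active arm and 2n controls, the unpooled variance is

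v = 0.35 x 0.65/(2n) + 0.245 x 0.755/n

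The expected final statistic is 0.105/sqrt(v), and the expected interim statistic is that times sqrt(0.5). Power is P(Z1 > 2.693) + P(0 < Z1 < 2.693 and Z2 > 1.904), with correlation sqrt(0.5).

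| Scale | 200/401 with outcomes | 211/422 with outcomes |
|---|---|---|
| Risk difference, unpooled | 79.1% | 81.1% |
| Risk difference, pooled | 76.0% | 78.0% |
| Log odds ratio | 75.6% | 77.6% |

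On the unpooled scale, which comes closest to the stated 80%, the two readings lie about one point on either side of it. Exactly 80% needs 206 per active arm with outcomes: 6 x 206 = 1236 without loss, or 1236/0.95 = 1301.1, so 1302, with it. Both are within 3% of 1266. The calculation does not separate the two readings.

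**The case against.** **The trigger can be met in practice.** The article never calls 1266 a cap, and the trigger is a minimum, so enrolment could run on. Dropping an arm can bring the trigger within 1266 (step 4). A reader might infer that the trial can never reach its final analysis, or must breach an approved size; the article supports neither. What stands is that no larger recruitment target is stated, and that 1266 is quoted for the 2:1:1:1:1 case, in which all four active arms continue.

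**Loss may be below 5%.** Children who miss the last visit are traced at home or by phone, and a child who dies or is hospitalised earlier already has a primary outcome. This reduces the gap but does not close it: with four active arms continuing, any loss leaves 1266 randomised short.

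**The loss clause is conditional.** It refers to all arms starting together, which will not happen, so the per-arm rule may be the operative one. That is fair, but the rule uses the per-arm counts that the conditional total breaks down into.

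**The origin of the mismatch.** A reader might infer that the trigger mistakenly took the loss-inflated figure as evaluable. Step 5 does not support that. It is as open that 211/422 were meant as evaluable and the loss clause is the misstatement.

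**The interim count.** Since 106 is about half of 211, a reader might want it reduced as well. The Interim analysis section counts participants, not children with outcomes, so nothing there conflicts.

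**The article is condensed.** The full protocol may state a randomised target. The point here is not an omission, however: the conflicting figures are all in the article.

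**Conclusion.** The point holds as an inconsistency between a sample size and an analysis trigger. With all four active arms continuing and any loss, the Sample size and Final analysis sections cannot both be met at 1266. At 5% loss the gap is about 63 children with data, or 67 to 71 more to randomise. With an arm dropped, the per-arm trigger may be met, but the abstract's sentence still cannot be if 1266 are randomised and any are lost.

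It should be corrected, but it does not make this a badly underpowered trial: the two readings differ by about 2 points of power. These figures assume 5% loss spread evenly over the arms, a simultaneous start, an interim at half information and the planning rates of 35% and 24.5%. The contradiction itself needs only the stated counts and a loss above zero.

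**What to change.** State whether 1266 (211 and 422) counts children randomised or children with the primary outcome, and align the abstract, the Sample size section and the Final analysis section.

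- **Cheapest version.** Keep 1266 as randomised. Start the final analysis when at least 211 children have been randomised to each continuing active arm and at least 422 to control, and all of them have reached their 24-week time point. Add that about 200 and 401 are expected to have the primary outcome, and restate power as about 79% on the unpooled risk difference. Reword the abstract to say randomised and followed to 24 weeks. Keeping the count per arm lets the rule work after an arm is dropped. The cost is wording and about one point of stated power.
- **Alternative.** If 211 and 422 are meant as evaluable, remove the statement that 1266 allows for 5% loss and give the larger randomised number, about 1333 to 1337. The cost is 67 to 71 more children. As an assumption on pace, 291 enrolled over about 10.5 months is about 28 per month, and the remaining 975 over about 28 months to September 2027 is about 35 per month. That means roughly 2 to 2.5 months of extra recruitment.

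Leave the interim count of 106 participants unchanged.

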#### Randomisation

The trial will begin with three arms active (control, antimicrobial and psychosocial) with a randomisation ratio of 2:1:1. The other two arms will be introduced when the reformulated RUTF has been developed (anticipated July 2025), and the ratio will be amended to rebalance towards the designed 2:1:1:1:1 ratio (standard-of-care, antimicrobial, reformulated RUTF, psychosocial and combined arms, respectively). The randomisation ratio may be altered a third time after the interim analysis if an arm is dropped to ensure a 2:1 ratio of standard-of-care vs each remaining intervention arm. Participants will be prospectively randomised sequentially using random permuted blocks with random block size, stratified by hospital site. The trial database will contain a secure, computer-generated, sequentially numbered randomisation list prepared by the trial statistician. If the caregiver has another child who has already been randomised in the trial, subsequent children will be automatically allocated to the same intervention. If a child has already been enrolled, s/he will not be eligible to re-enrol during a subsequent hospital admission.

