#### Interim analysis

One interim analysis will be undertaken once the following three conditions are achieved: (1) at least one active intervention arm reaches 106 participants; (2) the smallest active intervention arm reaches at least 50 participants; and (3) all four intervention arms are active. A logistic regression model accounting for country, age, sex and baseline oedema with indicators for each active treatment will be fitted on the composite primary outcome. If the test statistic falls below the lower (futility) bound of zero in an arm, indicating that there is no benefit of that arm over control, then that arm may be discontinued. Similarly, if the test statistic of an arm exceeds the upper (efficacy) bound (2.693), then that arm may be discontinued as it clearly suggests substantially lower mortality, hospitalisation or failed nutritional recovery than the control group. Active arms that have test statistics between the lower and upper bound will be continued, as they suggest potential benefit. The boundary estimates (0 and 2.693) have been calculated to control for the family-wise error. All decisions about dropping arms will be made in conjunction with the Data Monitoring and Ethics Committee, which comprises four independent members, and Trial Steering Committee, which comprises five independent members.

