### Time frame and study status

The trial has undergone ethical approval in Zimbabwe (Joint Research Ethics Committee for the University of Zimbabwe, Faculty of Medicine and Health Sciences & Parirenyatwa Group of Hospitals (206/2023); Medical Research Council of Zimbabwe (MRCZ/A/3064); and Medicines Control Authority of Zimbabwe (CT262/2023)); Zambia (University of Zambia Biomedical Research Ethics Committee (4266–2023); Zambia Medicines Regulatory Authority (CT135/24); and the National Health Research Authority (NHREB002/25/03/2024)); Kenya (Kenya Medical Research Institute (KEMRI) Scientific and Ethics Review Unit (KEMRI/CCR/CSC/0316/4808); Pharmacy and Poisons Board (ECCT/24/02/07) and the National Commission for Science, Technology & Innovation (NACOSTI/P/25/414674)); and the UK (Oxford Tropical Research Ethics Committee (44-23)). The trial Sponsor is Queen Mary University of London (EDGE ID 150522). Any protocol amendments will only be implemented after approval by regulators in each country and the Sponsor. The trial started enrolment in Zimbabwe and Zambia in July 2024 and in Kenya in March 2025. By 15 May 2025, a total of 291 children had been enrolled to the trial. The estimated date of the last participant enrolment is September 2027.

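### The primary model pools controls randomised before the reformulated RUTF and combined arms existed and has no term for randomisation period, so both late comparisons are open to calendar-time bias

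*Protocol article*

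**What the plan says.** All references are to the protocol article.

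- **Randomisation:** "The trial will begin with three arms active (control, antimicrobial and psychosocial) with a randomisation ratio of 2:1:1". Once the new product is available (anticipated July 2025), "the ratio will be amended to rebalance towards the designed 2:1:1:1:1 ratio". A further change is possible: "The randomisation ratio may be altered a third time after the interim analysis if an arm is dropped".
- **Time frame and study status:** enrolment began in July 2024 in Zimbabwe and Zambia and in March 2025 in Kenya. "By 15 May 2025, a total of 291 children had been enrolled to the trial".
- **Interim analysis:** "A logistic regression model accounting for country, age, sex and baseline oedema with indicators for each active treatment will be fitted". The bounds are 0 (futility) and 2.693 (efficacy).
- **Final analysis:** "The primary analysis will include all participants as randomised". The analysis is triggered by "at least 211 children in each active arm selected to continue to the second stage, and at least 422 control children". The model is "A logistic regression model with country, age, sex and oedema status as covariates, and a treatment indicator for each intervention, will be fitted", with a critical value of 1.904.
- **Sample size:** 1266 children, 80% power for a 30% relative reduction from 35%, one-sided family-wise error 0.10 and 5% loss. The calculation is stated to hold for all arms starting together.

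**The concern.** Allocation probability depends on calendar time by design. Before the new arms open, a child can receive control, antimicrobials or psychosocial support only. Randomisation therefore protects the reformulated RUTF and combined comparisons only within the later period. A single model on all randomised children, without a period term, compares these two arms with a control group that is partly historical.

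Drift in the event rate (changing case-mix, guideline uptake, staff experience, new sites) would be credited to the new arms if the rate falls and held against them if it rises. Two of the four primary comparisons are exposed, including the combined package, and they are exposed at both looks. The bounds 2.693 and 1.904 control family-wise error only if the event rate does not drift downwards.

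**Working it through.** **1. The plan's own figures.** A simulation of the four-arm, two-stage design used between-arm correlation 1/3 (2:1 allocation), equal information per stage and 2,000,000 runs. With bounds 0, 2.693 and 1.904 it gives family-wise error 0.0999 with binding futility and 0.101 non-binding. Pairwise power for 35% against 24.5% after 5% loss is 79.2% on an unpooled risk difference and 75.6% on the log odds ratio. The stated error control is right for a simultaneous start.

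**2. How many controls are non-concurrent.** 422 + 4 × 211 = 1266, which is the whole planned sample, so the 422 must include the early controls.

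- Documented count: 291 × 2/4 ≈ 146 controls; 146/422 = 35%. Each early arm has about 73.
- Left for the later period: 422 − 146 = 276 controls, 211 − 73 = 138 in each early arm and 211 in each new arm. Controls to a new arm run at 276/211 = 1.31:1, not 2:1.
- If 350 are enrolled by opening (assumption): 175 early controls (41%), leaving 247, or 247/211 = 1.17:1.
- At the interim, when an early arm reaches 106, there are about 2 × 106 = 212 controls. Of these 146/212 = 69% predate the new arms, which then have about 50 children each.

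**3. Hand check for a fall from 35% to 30%, no treatment effect, 146 early controls, no loss.**

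- Pooled control rate = (146 × 0.35 + 276 × 0.30)/422 = 0.3173; new-arm rate = 0.30.
- Odds ratio = (0.30/0.70)/(0.3173/0.6827) = 0.922; log = −0.081.
- SE = √[1/(422 × 0.3173 × 0.6827) + 1/(211 × 0.30 × 0.70)] = 0.183.
- Shift in Z = 0.081/0.183 = 0.443.
- One-sided error = 1 − Φ(1.904 − 0.443) = 0.072, against 1 − Φ(1.904) = 0.028.

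**4. Full two-stage simulation** (logistic model, 20,000 runs, 146 early controls, no treatment effect). The drift sizes are assumptions.

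| Event rate, early to late | Spurious OR, new arms | Error per new arm | FWER as written | FWER with period term |
|---|---|---|---|---|
| 35% to 35% | 1.00 | 0.026–0.028 | 0.097 | 0.099 |
| 35% to 32.5% | 0.96 | 0.043–0.046 | 0.123 | 0.094 |
| 35% to 30% | 0.92 | 0.070–0.072 | 0.162 | 0.095 |
| 35% to 25% | 0.83 | 0.160–0.163 | 0.295 | 0.092 |
| 30% to 35% | 1.08 | 0.008–0.010 | 0.065 | 0.095 |

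With 170 or 200 early controls, the fall from 35% to 30% gives FWER 0.183 or 0.209. With 175 early controls, 5% loss and the final test only, a fall from 40% to 35% gives about 0.078 per new arm and FWER about 0.17; 40% to 30% gives about 0.185 and 0.33.

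Error for the antimicrobial and psychosocial arms stays near 0.03 throughout. Their ratio to control is 2:1 in both periods (146:73, then 276:138), so both sides carry the same mix of periods.

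**5. Power if the rate rises from 30% to 35%** (146 early controls, true 30% reduction, final test only, no loss).

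- Pooled control rate = (146 × 0.30 + 276 × 0.35)/422 = 0.3327; new arm = 0.7 × 0.35 = 0.245.
- Log OR = −0.430, SE = 0.1905, Z = 2.254; power = Φ(2.254 − 1.904) = 64%.
- Without drift (35% against 24.5%): log OR = −0.506, SE = 0.1898, Z = 2.668; power = Φ(2.668 − 1.904) = 78%.

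**6. Power after the fix, no drift, two-stage simulation.** With 146 early controls, power for each new arm goes from about 77% to 72% with no loss, and from about 74% to 70% with 5% loss. With 170 early controls the adjusted figures are about 70% and 68%. The two early arms are unchanged (about 79% and 77%).

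**The case against.** - **Direction.** Error is inflated only if the event rate falls. With no drift the 0.10 holds; with a rise it shrinks and the late arms lose power. This is correct, and the point is put here as bias in either direction.
- **Size.** The documents give no drift estimate, and a fall of 2.5 points takes family-wise error only to 0.123. This stands: the figures are a range, not a forecast. But enrolment is planned to run from July 2024 to September 2027, and the plan gives no reason to expect a constant rate.
- **Existing covariates.** Country absorbs Kenya's later start. Age, sex and oedema take up some case-mix. In Zimbabwe and Zambia the first period covers about a full year, so season largely averages out there. This narrows the sources of drift but leaves change over time within a country, and season in Kenya.
- **Inferred counts.** The plan says it will rebalance towards the ratio, and the 422 and 211 are minima. Pooling is nevertheless what one model on all randomised children implies, and 1266 leaves no room to exclude the early controls.
- **Unseen analysis plan.** It may add a period term or a concurrent-control analysis. The article, however, prints an explicit covariate list for both models, so such a plan would contradict it and the two would have to be reconciled.

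**Conclusion.** The concern holds. As written, the interim and final models leave out the variable that governs allocation, and about 35% of the planned controls (41% if 350 children are enrolled before opening) could never have been allocated to the two late arms. The stated family-wise error of 0.10 for the trial as run depends on the event rate not falling over time. A 5-point fall takes it to about 0.16 to 0.21 for 146 to 200 early controls. A 5-point rise costs the late arms roughly 14 points of power.

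These sizes rest on assumed drift, on the later allocation being set to reach exactly 422 and 211, and on no arm being dropped. The antimicrobial and psychosocial comparisons are not materially affected while their ratio to control stays at 2:1. This should be settled before the interim analysis, where the non-concurrent share of controls is highest.

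**What to change.** 1. Add randomisation period as a categorical covariate to both the interim and the final logistic models: 2:1:1; five-arm rebalanced; post-interim if the ratio changes again. Define it by the ratio in force at the child's site on the day of randomisation, since countries may open arms on different dates.
2. Apply the 0, 2.693 and 1.904 bounds to the period-adjusted statistics.
3. Pre-specify a supporting analysis of the reformulated RUTF and combined arms against concurrently randomised controls only.
4. Restate power for these two arms under the staggered start, because the present calculation assumes all arms begin together.

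The period term returned family-wise error to 0.09–0.10 in every drift scenario tried. It needs only a change of wording in the protocol and analysis plan, and no extra children are needed to remove the bias. The cost is precision: power for the late arms is about 70–72% with no loss and 68–70% with 5% loss, for 146 to 170 early controls. If the sponsor wants 80% for these arms, more children would be needed in the later period, and that decision should be made openly.

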## Methods and analysis

### Trial setting

The Co-SAM trial is being undertaken at nine sites in three countries. In Zimbabwe, where the prevalence of wasting is 2%,^29^ three hospitals in Harare (Sally Mugabe Children’s Hospital, Parirenyatwa Hospital and Chitungwiza Central Hospital) serve a predominantly urban and peri-urban population, although some children are referred for inpatient care from rural districts. In Zambia, the University Teaching Hospital Children’s Hospital (UTHCH) in Lusaka provides secondary level services to the city of Lusaka (population 1.9 million, census 2022) and tertiary level services to the whole country (population 19 million). The child malnutrition ward in UTHCH provides inpatient care for children with complicated SAM, most of whom are drawn from high-density urban and peri-urban residential areas of the city. Matero Level 1 hospital provides primary and secondary level care for the high-density areas of north-west Lusaka. The prevalence of SAM in Zambia was 1.5% in 2018.^30^ There are four hospitals in Kenya: Migori County Hospital and Homa Bay County Teaching and Referral Hospital serve a rural area in Western Kenya; Coast General Teaching and Referral Hospital, Mombasa serves an urban and peri-urban population on the coast; and Mbagathi sub-County Hospital predominantly serves a population living in informal settlements in Nairobi. The prevalence of acute malnutrition among under-5 children in Kenya in 2022 was 4.9%.^31^

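### Randomisation is stratified by hospital site, but the interim and final models adjust only for country, leaving within-country site differences unadjusted at a small cost in power

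*Protocol article*

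**What the plan says.** Under Randomisation, the protocol article says: "Participants will be prospectively randomised sequentially using random permuted blocks with random block size, stratified by hospital site". Under Trial setting it says: "The Co-SAM trial is being undertaken at nine sites in three countries". The list that follows gives three hospitals in Zimbabwe, two in Zambia and four in Kenya.

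The Interim analysis section reads: "A logistic regression model accounting for country, age, sex and baseline oedema with indicators for each active treatment will be fitted". The Final analysis section specifies "A logistic regression model with country, age, sex and oedema status as covariates", plus one indicator per intervention arm. Secondary outcomes follow the same principles.

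The stratification factor therefore has nine levels, and the geographical covariate in both models has three. The covariate list is written out twice, so this is a stated choice and not a detail left for the SAP.

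Two other statements matter for the late arms. First, "The trial will begin with three arms active (control, antimicrobial and psychosocial) with a randomisation ratio of 2:1:1". The reformulated RUTF and combined arms join later, and the ratio is then amended towards 2:1:1:1:1. Second, Time frame and study status gives start dates by country: Zimbabwe and Zambia in July 2024, Kenya in March 2025.

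**The concern.** Blocking by site makes the arms nearly balanced on site. That balance reduces the true variance of the treatment comparison, but the model-based standard error reflects the reduction only if the model contains site. When site is omitted, variation between sites stays in the error term. The test statistic is then somewhat too small, and the test is conservative. The logistic odds ratio also moves slightly towards 1.

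There is reason to expect some variation within countries. In Kenya, two hospitals serve a rural western area, one serves an urban and peri-urban coastal population, and "Mbagathi sub-County Hospital predominantly serves a population living in informal settlements in Nairobi". The primary composite counts any overnight admission (Table 1), which can depend on local access and admission practice.

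What is at stake is a little power in each of the four comparisons, in a design with little to spare.

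The late arms raise a second question. Their children come only from the later period, while the controls come from both periods, and no restriction to concurrent controls is stated. If the share of children from each site within a country changed over time, a country term would not correct for it.

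**Working it through.** **Inputs from the protocol article.** Control rate 35%; 30% relative reduction, so 0.35 × 0.70 = 24.5%; 422 controls and 211 per active arm (422 + 4 × 211 = 1266); bounds 0 and 2.693 at the interim and 1.904 at the end; one-sided family-wise error 0.10; 5% loss; nine sites split 3/2/4. **Assumed, because not given:** the site standard deviation (SD) on the logit scale.

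**1. The plan's own figures.** A simulated two-stage, four-arm design (10^6 draws, correlation 1/3 from the shared control, interim at half the information) gives a family-wise error of 0.0996 against the stated 0.10. Power for one effective arm is 0.80–0.81 at 422/211 with unpooled variance and 0.78–0.795 after 5% loss. With the log-odds variance it is 0.77–0.78 at 422/211. The stated design reproduces, with no slack.

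**2. Size by hand.** On the log-odds scale the effect is ln(0.35/0.65) − ln(0.245/0.755) = 0.506. Its standard error is √[1/(422 × 0.35 × 0.65) + 1/(211 × 0.245 × 0.755)] = 0.190, so the expected z is 2.668. At 1.904 the one-sided error is 0.0285 and the single-look power is Φ(2.668 − 1.904) = 0.777.

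With equal-sized sites, country removes 3 of 9 parts of the site variance and leaves (9 − 3)/9 = 6/9. The share of outcome variance left in the error is about R² = 0.35 × 0.65 × SD² × 6/9. With arms balanced within site, omitting site acts as if the critical value were 1.904/√(1 − R²).

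| Site SD | R² | Effective critical value | One-sided error | Power | Loss (points) |
|---|---|---|---|---|---|
| 0.3 | 0.014 | 1.917 | 0.0276 | 0.774 | 0.4 |
| 0.5 | 0.038 | 1.941 | 0.0261 | 0.766 | 1.1 |
| 0.6 | 0.055 | 1.958 | 0.0251 | 0.761 | 1.7 |
| 0.7 | 0.074 | 1.979 | 0.0239 | 0.754 | 2.3 |

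**3. Simulation, stable site mix.** With 400 v 200 children and treatment balanced within site (2,500 trials each), power with country v site adjustment was 76.9% v 77.6% (SD 0.3), 77.1% v 78.1% (0.5) and 75.0% v 77.3% (0.7). The gains are 0.7, 1.0 and 2.3 points. Each power figure has a Monte Carlo standard error of about √(0.77 × 0.23/2500) = 0.8 points. Both models were fitted to the same trials, so the differences are more precise than that.

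**4. Simulation with staggered arms.** Trials of 1266 children had three arms first and five later, site-stratified allocation, and start dates staggered by country only, as documented.
- One-sided error (9,000 trials), SD 0.3: country 0.0275 for the early arms and 0.0298 for the late arms; site 0.0283 and 0.0309.
- One-sided error, SD 0.6: country 0.0253 for both; site 0.0286 and 0.0290.
- Power (1,500 trials), SD 0.6: early arms 0.752 with country v 0.772 with site; late arms 0.738 v 0.753. Up to SD 0.4 the gain stayed under 1 point.

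The Monte Carlo standard error of each error rate is at most √(0.0285 × 0.9715/9000) = 0.0018.

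**5. Late arms under an extreme shift.** Here the site mix within country was also made to change strongly between the two periods, which the document does not describe.
- SD 0.6: late-arm error 0.039 with country v 0.026 with site; power 0.716 v 0.754.
- SD 0.3: late-arm error 0.029 v 0.027, which is no material difference.

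**6. Can the model carry nine sites?** The average is 1266/9 = 141 children per site. Events lie between 422 × 0.35 + 844 × 0.245 = 355 (all arms effective) and 1266 × 0.35 = 443 (none effective). Eight site terms, four treatment terms, age, sex and oedema make 15 coefficients, or at least 355/15 = 24 events each.

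**The case against.** The strongest defence is that country is a coarser grouping of the same factor. Each site lies in one country, so the between-country part of the site effect is already adjusted. A reader might infer that the analysis ignores the randomisation design. It does not; it uses part of it. This stands.

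A reader might also infer that the reformulated RUTF and combined arms are confounded by site mix. The document does not support that. It describes staggered starts by country only, and the country term deals with those. Inflated error appeared only when a large site SD was combined with an assumed, extreme shift in site mix within country. The risk is conditional. The more direct consequence of late-opening arms, drift in outcome over calendar time, is a separate matter that a site term would not remove.

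The smaller odds ratio under country adjustment is not bias. With arms balanced within site it reflects non-collapsibility: the two models estimate different odds ratios, and the null hypothesis is the same for both.

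Finally, Trial setting describes catchments and hospital level, not outcome rates. The three Zimbabwe hospitals are described together, and both Lusaka hospitals draw largely on dense urban areas. Only Kenya shows a clear contrast. No site SD can be read from the document, and values near 0.7 may be too large. At an SD of 0.3, conservatism is barely visible.

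These points limit the size of the problem. They do not explain why the model departs from the stratification factor, and the document offers no reason.

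**Conclusion.** The mismatch is real and is fixed in the text of both the interim and final analyses, but its consequences are small. For assumed site SDs of 0.3 to 0.7, the country-only model is at most slightly conservative and loses roughly 0 to 2 points of power. The hand calculation and two separate simulations agree on this. False-positive error is not inflated while the site mix within country is stable. Late-arm bias remains a conditional risk.

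The result rests on assumed site variation, near-balance of arms within site, roughly equal site sizes in the hand calculation, and a single final look at 1.904. The change is worth making because it costs almost nothing and analyses the trial by the groups within which it randomises.

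**What to change.** Replace country with hospital site (nine levels, as a fixed or random effect) in the interim and final primary models and in the secondary outcome models. State in the SAP, before the interim, a rule for pooling very small sites with another site in the same country. The rule matters most at the interim, when sites are smaller.

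Site is already recorded as the stratification factor, and the sample size does not change. The cost is SAP and protocol wording, plus amendment approval by the regulators and sponsor if the full protocol fixes the covariates (Time frame and study status requires such approval). Calendar-time drift needs its own provision and should not be treated as solved by this change.
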